### Setting

The study will take place in Auckland, New Zealand. Non-fasted blood samples will be collected at the North Shore or Waitakere Hospitals in Auckland, New Zealand. Questionnaires and anthropometry will be undertaken at Massey University, Auckland, New Zealand. Auckland is New Zealand’s largest city with a population of just over one million. It has been estimated that approximately 13,000 (32.5 %) individuals with ASD reside in the Greater Auckland region [1].

### Stage 1 – screening

Screening and recruitment (stage 1 of the study) will take place over a 24-month period, which commenced in January 2015. Children who meet the initial inclusion criteria will have a blood draw and will be screened for nutritional deficiencies. See Tables 1 and 2 for outcome measures, testing methods, and schedule of enrolment, intervention, and assessment, respectively.

**Table 1 Tab1:** Summary of the study outcome measures and methods

Variables	Methods
Blood analysis^a^	
25(OH)D	Serum: Siemens ADVIA Centaur Vitamin D Total assay
RBC fatty acids	Erythrocytes: Shimadzu GC-17A flame-ionisation gas chromatography (Rydalmere, NSW, Australia)
Calcium	Serum: Siemens Dimension Vista® System. CA Flex® reagent cartridge, Cat. No. K1023
Albumin	Serum: Siemens Dimension Vista® System. ALB Flex® reagent cartridge, Cat. No. K1013
Iron studies	Ferritin, serum: Siemens Dimension Vista® System. FERR Flex® reagent cartridge, Cat. No. K6440
	Iron, serum: Siemens Dimension Vista® System. IRON Flex® reagent cartridge, Cat. No. K3085
	Total iron binding capacity, serum: Siemens Dimension Vista® System. TIBC Flex® reagent cartridge, Cat. No. K3084
Vitamin B_12_	Serum: Siemens Dimension Vista® System. B12 Flex® reagent cartridge, Cat. No. K6442
Folate	Serum: Siemens Dimension Vista® System. FOL Flex® reagent cartridge, Cat. No. K6444
Full blood count	Whole blood: Sysmex XE-5000™ Automated Haematology System
Vitamin A	Plasma:, Shimadzu Prominence Modular HPLC System. Cat. No. LC-20A. The assay was developed at Massey University
Questionnaires	
Primary outcome measures	
Sociocommunicative functioning	Social Responsiveness Scale-second edition (SRS-2) [73]. Completed by caregiver at Massey University
Sensory problems	Sensory Processing Measure (SPM) [75]. Completed by caregiver at Massey University
Problem behaviours	Aberrant Behaviour Checklist-Community (ABC-C) [78]. Completed by caregiver at Massey University
Secondary outcome measure	
Gastrointestinal symptoms	A questionnaire and diaries completed by caregiver
Other measures	
Sociodemographics	Completed by caregiver
Medical history	Completed by caregiver
Dietary assessments	Dietary Index Children’s Eating (DICE). Completed by caregiver
	Feeding issues and mealtime behaviours (Behavioural Paediatrics Feeding Assessment Scale, BPFAS). Completed by caregiver
	Four-day estimated food diary. Completed by caregiver. Analysed using FoodWorks 2007 (Xyris Software)
	Nutritional supplements and special dietary regimens. Completed by caregiver
Sun exposure and skin colour	Completed by caregiver
Medication/supplement use/incidence of adverse events and supplement compliance	Diary completed by caregiver
Anthropometry	Weight: Tanita electronic scale; Height: Stadiometre; measured by researcher at Massey University

*25(OH)D* 25-hydroxyvitamin D, *HPLC* high-performance liquid chromatography, *RBC* red blood cell

^a^All blood samples are collected and analysed at the North Shore and Waitakere Hospitals

**Table 2 Tab2:** Schedule of enrolment, intervention, and assessment

	Study period						
	Enrolment		Allocation	Post allocation			
Timepoint	t_−2_	t_−1_	t_0_	t_baseline_	t_6-month_	t_12-month_	w_1–52_
Enrolment:							
Initial eligibility screen	♦						
Informed consent	♦						
Nutritional deficiencies screen		♦					
Allocation			♦				
Interventions:							
Vitamin D				♦	♦	♦	
Omega-3 LCPUFAs				♦	♦	♦	
Vitamin D + omega-3 LCPUFAs				♦	♦	♦	
Placebo				♦	♦	♦	
Assessments:							
Nutritional biomarkers							
Serum 25(OH)D				♦	♦	♦	
RBC fatty acids				♦		♦	
Calcium				♦	♦	♦	
Albumin				♦	♦	♦	
Iron studies				♦			
Vitamin B_12_				♦			
Folate				♦			
Full blood count				♦			
Vitamin A				♦			
Primary outcome							
Social Responsiveness Scale-2				♦		♦	
Sensory Processing Measure				♦		♦	
Aberrant Behaviour Checklist				♦		♦	
Secondary outcome							
Gastrointestinal symptoms				♦		♦	♦
Dietary assessment							
Dietary Index Children’s Eating				♦		♦	
Behavioural Paediatric Feeding Assessment Scale				♦		♦	
4-day food diary				♦			
Nutritional supplements and dietary regimen				♦			
Other assessments							
Sociodemographics				♦			
Medical history				♦			
Sun exposure and skin colour				♦			
Compliance and adverse events diary							♦

*25(OH)D* 25-hydroxyvitamin D, *t* timeline, *w* week, *LCPUFA* long chain polyunsaturated fatty acid

According to the SPIRIT statement: Defining Standard Protocol Items for Clinical Trials

### Pre-intervention preparation

Prior to randomisation and inclusion in the trial, vitamin D, iron and vitamin B_12_ deficiencies will be addressed. Refer to Table 3 for a list of nutritional deficiencies and the management strategies applied in this trial.

**Table 3 Tab3:** Nutritional deficiencies and their management strategies prior to entering the intervention trial

Nutritional deficiency	Management
Vitamin D	Participants with serum 25(OH)D concentrations <25 nmol/L will be offered supplementation of 400 IU per day^a^
Iron	Children with iron deficiency will be offered iron supplements and postponed entry into the trial after 3 months. Children will not be retested A child will be iron deficient when two of the following pools are abnormal: red cell pool (haemoglobin <111 g/L, red blood cell distribution width >14 %), transport iron (iron saturation <16 %) and/or storage iron (serum ferritin ≤15 μg/L)^a^. Criteria for treatment will be according to the New Zealand Ministry of Health guidelines^b^
Vitamin B_12_	Children with serum levels <110 pmol/L will be offered the option of prescribed supplements or dietary advice to improve status

^a^New Zealand Ministry of Health 2015 [83]

^b^Retrieved from https://www.starship.org.nz/for-health-professionals/starship-clinical-guidelines/i/iron-deficiency/on 5 March 2015

### Stage 2 – vitamin D and n-3 LCPUFA intervention

The intervention consists of 2000 IU of vitamin D_3_ per day, 722 mg of DHA per day, 2000 IU of vitamin D_3_ plus 722 mg of DHA per day or placebo, in the form of four oral capsules. The treatment materials will be delivered in 750-mg gel capsules with a tear-off nozzle manufactured and supplied by Douglas Nutrition Ltd., Auckland, New Zealand. The study capsules, vitamin D, n-3 LCPUFAs and placebo are identical in appearance and all are tasteless and colourless. The child is required to consume the contents of four capsules per day mixed into their food of preference or by oral administration by syringe. Refer to Table 4 for the total daily intake and contents of each capsule. Throughout the study period, children are allowed to have any therapy or medication for autism as well as any supplement provided that it does not contain vitamin D or omega-3.

**Table 4 Tab4:** Total daily intake of vitamin D and omega-3 long chain polyunsaturated fatty acids (n-3 LCPUFAs) and the contents of each capsule, vitamin D, n-3 LCPUFAs and placebo

Treatment groups	Daily intake
Vitamin D	2 × 750-mg capsules of olive oil, 2 × 1000-IU capsules of vitamin D_3_ in medium-chain triglycerides (MCT), alpha tocopherol
N-3 LCPUFAs	2 × 750-mg capsules of olive oil, 2 × high-DHA triglyceride fish oil capsules (total DHA dose = 722 mg/day), alpha tocopherol
Vitamin D and n-3 LCPUFAs	2 × 1000-IU capsules of vitamin D_3_ in 750 mg MCT, 2 × high-DHA triglyceride fish oil capsules (total DHA dose = 722 mg/day), alpha tocopherol
Placebo	750-mg capsules of olive oil plus alpha tocopherol (antioxidant)

*DHA* docosahexaenoic acid, *MCT* medium-chain triglycerides

Supplementation with 2000 IU vitamin D_3_ has been shown to be a safe dose in infants [67, 68], and the French Society of Paediatrics recommends 1000 to 1200 IU per day in breast-fed infants [69]. The body mass of 2.5–8 year-olds in our trial will be considerably greater than infants’, which should further reduce the risk of adverse events. Furthermore, 2000 IU per day is less than the safe upper limit of 2500 and 3000 IU/day suggested by the IOM for 1–3 and 4–8 year age groups, respectively [70].

The DHA dose of 722 mg/day is physiologically relevant and achievable through diet (equivalent to approximately three servings of fatty fish per week) and is comparable to doses used in other trials in children investigating the effects of n-3 LCPUFAs on behaviour and learning [71]. No side-effects have been reported in children with a dose of 600 mg DHA/day [72].

### Randomisation, blinding and concealed allocation

Children will be randomly allocated to one of four groups, having been stratified for age and severity of ASD. Randomisation of the active/placebo capsules, the randomised sequence list, and group assignment will be fully concealed from the researchers, children and caregivers for the entire study, including the data analysis. A third party not involved in any aspects of the study will generate a random block design in blocks of four and eight using Randomization.com (http://www.randomization.com/). The third party will allocate a treatment code to a child once their eligibility for the intervention is confirmed and the caregiver’s consent is received. In an emergency situation where breaking of the study blind will be required, plans will be in place for the principal investigator to contact the third party responsible for randomisation to reveal the treatment assignment for a given participant.

### Data collection

Participants (caregivers and children) will attend the Human Nutrition Research Unit (HNRU) at Massey University on two occasions: baseline and 12 months. Once recruited into stage 2 and prior to being given a 4-month supply of supplements, caregivers will complete some questionnaires on core symptoms of ASD (sociocommunicative functioning and sensory issues) and aberrant behaviours as the study primary outcome measures, and on gastrointestinal symptoms as the secondary outcome measure. Once the intervention is completed (12 months), baseline assessments of core symptoms of ASD and aberrant behaviours completed by caregivers will be repeated. Caregivers will also complete weekly gastrointestinal symptom diaries over the study period.

Further information will be collected to describe the study population characteristics at the baseline. This information includes eating/mealtime behaviours, food diaries, sun exposure, skin colour and anthropometry (weight and height). At the final visit, baseline assessment of eating/mealtime behaviours will be repeated and children’s weight/height will be measured. Refer to Table 1 for outcome measures and testing methods.

### Blood sampling and analysis

Children will have their blood samples drawn on three occasions, baseline (stage 1 – screening), 6 months (safety measures) and 12 months (endpoint). Refer to Table 1 for nutritional biomarkers and testing methods. The non-fasted blood samples will be collected under the supervision of paediatric staff and processed at North Shore or Waitakere Hospitals of WDHB laboratory service. Nutritional biomarkers will be assayed from a venous blood sample. These include the following: 25(OH)D, RBC fatty acids, calcium, albumin, iron studies, vitamin B_12_ and folate, full blood count and vitamin A. With the exception of RBC fatty acids and vitamin A, all biomarkers will be analysed at North Shore Hospital. RBC fatty acids will be analysed at the University of Wollongong, NSW, Australia, and vitamin A in a laboratory at Massey University, Auckland, New Zealand.

### Questionnaires

The primary outcome measures are psychological assessments of core symptoms of ASD and co-occurring problem behaviours which are detailed in Table 1. The secondary outcome measure is the assessment of gastrointestinal problems. Standardised instructions will be given to all caregivers on how to complete the questionnaires during their visit to the HNRU. Before the participant departs the HNRU researchers check all answers for completeness.

*Social Responsiveness Scale**™**, Second Edition (SRS-2)* [73]: the SRS-2 versions specific for age groups 2.5–4.5 and 4.5 through 18 years will be used. SRS-2 identifies social impairment associated with ASDs and quantifies its severity in the domains of social awareness, social information processing, reciprocal social communication, social anxiety/avoidance, and stereotypic behaviour/restricted interests [73]. The clinical validity and sensitivity of SRS-2 has been determined in populations with ASD [74].

*Sensory Processing Measures**™**(SPM)* [75]: the SPM versions specific for age groups 2–5 and 5–12 years will be used. SPM assesses sensory processing, planning and ideas (praxis) and social participation in children. The scales measure social participation, vision, hearing, touch, body awareness (proprioception), balance and motion (vestibular function) and planning and ideas (praxis) [75]. This tool has been standardised, validated and used in children with ASD [76, 77].

*Aberrant Behaviour Checklist (ABC)* [78]: the ABC measures the variety of behaviour problems, namely irritability, social withdrawal, stereotypic behaviour, hyperactivity and inappropriate speech [79]. It has been validated in children with ASD [80] and has been widely used in treatment outcome studies of ASD [40].

*Gastrointestinal symptoms questionnaire*: the gastrointestinal symptoms questionnaire is designed specifically for this study and includes gastrointestinal signs and symptoms most commonly reported in children with ASD [81, 82]. Caregivers of study participants will be provided with weekly online diaries and will be asked to record if the child had constipation, diarrhoea, flatulence, abdominal pain, vomiting/nausea, abdominal distension, unexplained daytime irritability or/and unexplained night-time awakening during the past week, and if so how many times these occurred. The gastrointestinal symptoms questionnaire has not been validated, but includes questions on gastrointestinal symptoms most widely reported in ASD populations, or behaviours that might be a consequence of gastrointestinal symptoms. We are not aware of a validated instrument for assessing gastrointestinal symptoms in autistic children, and certainly not in New Zealand.

*Dietary Index of Children’s Eating (DICE)*: the DICE is a simple diet-quality assessment tool which has been developed by the research team, based on the New Zealand Ministry of Health Food and Nutrition Guidelines for Healthy Children and Young People [83]. This tool has been validated in a cohort of New Zealand healthy children aged 2 to 8 years (unpublished), and will be validated in ASD children in this study against the 4-day estimated food diary and biochemical markers.

*Behavioural Paediatrics Feeding Assessment Scale (BPFAS)*: the BPFAS is a simple assessment tool which measures a child’s mealtime behaviour and parents’ attitudes and behaviours. It is a 35-item scale questionnaire comprising 25-likert scale (5 points) questions about child behaviour and 10 dichotomous questions about parents’ attitudes and behaviours. Cut-off scores for the BPFAS have recently been established [84]. The BPFAS is the most reliable parent-administered feeding questionnaire, with good internal validity and test-retest reliability [85].

*Four-day estimated food diary*: dietary intake data will be collected by a 4-day estimated food diary, including one weekend day. Instructions on how to accurately complete the food diary will be provided with the food diary. Participants will be given a free-post, pre-addressed envelope for the return of the booklet. Average macro and micronutrient intake will be assessed over four reported days using FoodWorks Professional Edition 7 (Xryis Software, Brisbane, QLD, Australia, 2012).

In the present study, a 4-day food diary was chosen because of the high respondent burden and time-consuming characteristics of longer food diaries such as a 7-day food diary. Because of the high within-person variation in nutrient intakes, it is recommended to record dietary intakes over a longer period of time to have a highly accurate estimate of intake. However, if a 4-day food diary covers different days randomly, it can provide accurate estimates of dietary intake [86].

Information regarding sun exposure and skin colour, nutritional supplements and any special dietary regimens followed will be collected by questionnaires specifically designed for the purpose of the current study. The sun exposure questionnaire includes a question on caregiver’s beliefs and attitudes toward sun exposure as well as questions on country and city of residency in pregnancy, season of birth and child’s sensitivity to temperature and light extremes.

### Compliance to medication/adherence to study protocol

Caregivers will receive weekly emails containing a link to the online compliance and gastrointestinal issues diary and a tip/fact about autism and nutritional matters. Caregivers will be contacted by telephone at 1, 3, 6 and 9 months for morale purposes and to encourage compliance. Caregivers also will receive quarterly trial newsletters. The newsletters will include an update on the study, generic topics about ASD, a caregiver’s experience in relation to that topic, and entertainments/competitions for the study children.

New intervention materials will be sent out to participants every 4 months and caregivers will be asked to place the bottles from the previous months aside, with any unused capsules in them, to be returned at their next visit (6 or 12 months) at which stage unused capsules will be counted and recorded. Compliance to treatment will be analysed by counting each participant’s remaining supplements once they have completed the intervention.

### Adverse events

All participants will be recalled at 6 months for a blood test to check for hypervitaminosis D (serum 25(OH)D >225 nmol/L) and hypercalcaemia (serum Ca >2.7 mmol/L). Results will be checked by a third party who is unblinded (but has no involvement in analysis of results). The third party will de-identify blood test results and send them to the trial paediatrician and senior investigator for review and recommendation if the child’s serum 25(OH)D or calcium level is above the safe upper limit. If 25(OH)D concentrations are at or approaching 225 nmol/L, or if hypercalcaemia is present, dose administration will be adjusted.

Compliance and gastrointestinal symptom diaries will be monitored on a weekly basis and all side effects will be recorded in the adverse events log to keep a track of the child’s general health and behavioural reactions. In the case of any adverse events, the child’s health will be monitored more closely for three to four consecutive weeks, and if the adverse event persists, the reports will be referred to the trial paediatrician and senior investigator for further investigation.

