**Fig. 1 Fig1:**
[figure not shown]
Schematic diagram of study design. ^1^Blood biomarkers: 25-hydroxyvitamin D (25(OH)D), red blood cell (RBC) fatty acids, calcium, albumin, iron studies, vitamin B_12_, folate, full blood count and vitamin A. Questionnaires: sociodemographics, medical history, eating/mealtime behaviours and food diary. ^2^Questionnaires: sociocommunicative functioning, sensory problems and aberrant behaviours (primary outcomes); gastrointestinal symptoms (secondary outcome), sun exposure and skin colour. Anthropometry: weight and height. ^3^Blood biomarkers: 25(OH)D, RBC fatty acids, calcium and albumin. Questionnaires: sociocommunicative functioning, sensory problems, aberrant behaviours (primary outcomes) and eating/mealtime behaviours and diet quality. Anthropometry: weight and height. ^4^Blood biomarkers: 25(OH)D, calcium and albumin. *Gastrointestinal symptoms (secondary outcome) and medication/supplement use/incidence of adverse events/supplement compliance will be monitored throughout the study period

Stage 1 will provide the opportunity for a comprehensive description of the study population with respect to nutritional status (biochemical indices and dietary intake), demographics and medical history. Stage 2 will demonstrate the efficacy of supplementation with vitamin D, n-3 LCPUFAs or both on reducing ASD symptoms.

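### The adverse event rule makes referral of any clinical event wait three to four weeks and depend on persistence, with no exception for serious events

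*Protocol article*

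**What the plan says.** The Adverse events section of the protocol article describes two safety routes.

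- **Laboratory route.** "All participants will be recalled at 6 months for a blood test to check for hypervitaminosis D" and hypercalcaemia. If a level is above the safe limit, an unblinded third party "will de-identify blood test results and send them to the trial paediatrician and senior investigator for review and recommendation". The dose is adjusted if 25(OH)D reaches or approaches 225 nmol/L or if hypercalcaemia is present. No waiting period is stated.
- **Clinical route.** Caregiver diaries are reviewed weekly and side effects go into an adverse events log. The rule that follows opens with "In the case of any adverse events" and says that the child "will be monitored more closely for three to four consecutive weeks, and if the adverse event persists, the reports will be referred", the recipients being the trial paediatrician and senior investigator.

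Other places bear on how far the clinical rule reaches. The Fig. 1 legend says that "incidence of adverse events/supplement compliance will be monitored throughout the study period". Table 1 has a row for "Medication/supplement use/incidence of adverse events and supplement compliance", recorded in a caregiver diary, and Table 2 schedules a compliance and adverse events diary over weeks 1 to 52. Under Questionnaires, the weekly gastrointestinal diary lists "constipation, diarrhoea, flatulence, abdominal pain, vomiting/nausea, abdominal distension", together with unexplained irritability and night waking.

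**The concern.** The clinical rule joins a wait to a condition and applies both to every event. Neither depends on how serious the event is. Staff who followed it to the letter would hold a serious event for three to four weeks before asking for medical review, and would have no instruction to refer one that had settled by then.

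The participants are children aged 2.5 to 8 years who take supplements for 12 months, and day-to-day safety information comes mainly from caregiver diaries. Whether a serious event prompts further investigation, or a decision about continuing the supplement, should turn on its seriousness and not on how long it lasts.

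**Working it through.** The plan gives no figure to reproduce here. The check is a reading of the rule against the rest of the article, plus one conversion of units.

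**Step 1. Take the rule apart** (Adverse events section).
- Scope: all adverse events, with no grading by seriousness or severity.
- Wait: three to four consecutive weeks of closer monitoring, i.e. 3 × 7 = 21 days to 4 × 7 = 28 days.
- Condition for referral: the event persists.
- Recipients: the trial paediatrician and senior investigator.

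**Step 2. Is the scope really that wide?** The gastrointestinal diary items alone would make the rule a sensible one for minor complaints. But the Fig. 1 legend and Tables 1 and 2 record adverse events in general. The Adverse events section itself gives the purpose of the log as following the child's general health and behavioural reactions. The rule is not confined to gut symptoms.

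**Step 3. Look for an exception elsewhere.**
- The laboratory route has no stated wait, but it is triggered by 25(OH)D or calcium and not by a clinical event.
- The emergency provision under Randomisation, blinding and concealed allocation is not subject to the wait. It governs breaking the code, however, and sets no referral route or timing for adverse events.
- On the 6-month blood draw, the Blood sampling and analysis section says "The non-fasted blood samples will be collected under the supervision of paediatric staff". The stated purpose of that recall is the 25(OH)D and calcium check.
- No section of the article defines a serious event or sets a separate route for one.

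**Step 4. Apply the rule to the four possible cases.**
- Non-serious, settles within the watch: logged and watched, not referred. Reasonable.
- Non-serious, persists: referred after 21-28 days. Reasonable.
- Serious, persists: referred after 21-28 days. Too late.
- Serious, settles within the watch: meets no stated referral condition. A gap.

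**Step 5. Compare with referral on receipt.** The time from receipt of the report to referral falls from 21-28 days to 0, a difference of 21-28 days for the third case. The fourth case gains a referral that it otherwise lacks. Any delay between onset and the diary report is not stated in the article. It would add equally to both sides, so it drops out of the difference.

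**The case against.** The strongest answer is that this is a condensed journal article. Definitions of serious events and expedited reporting commonly sit in the full protocol, and their absence here would be no fault. That is right as far as it goes, and silence would not have been worth raising. But the article is not silent. It states a rule for all events that delays referral and makes it depend on duration. If the full protocol has a serious-event procedure, the article's wording conflicts with it and needs aligning.

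A second answer is context. The rule follows directly on the sentence about weekly diary review, so its natural subject is side effects found in the diaries, many of them minor. This narrows the concern but does not remove it, because the same diaries and log take in adverse events of every kind.

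A third answer is that the rule is not passive. Closer monitoring is required, the diary comes in weekly, emergency unblinding is available at once, and raised 25(OH)D or calcium goes to the paediatrician with no stated wait. All of this stands. A reader might infer that a child with a serious event goes unobserved for a month, or that staff may not refer early. The documents support neither inference: observation continues, and nothing bars earlier referral. What is missing is an instruction to refer.

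Finally, little suggests that serious events will be common. The article places the vitamin D dose below the upper limits that it cites for both age bands, and reports no side-effects in children at 600 mg DHA per day (the trial gives 722 mg). This bears on how often the rule would matter, but it does not exclude serious events, including ones unrelated to the supplements.

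**Conclusion.** The point holds as a fault in a stated safety rule. Read as written, a serious or severe clinical event that continues is referred only after 21-28 days of closer monitoring, and one that settles sooner has no stated referral. The 21-28 days is the only figure that the text supports. No rate of serious events is given, so the number of children affected cannot be estimated and may be small.

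The conclusion rests on reading the scope of the rule literally, and on the article containing no other referral trigger for clinical events, which the check above bears out. It does not rest on any claim about what staff would do in practice.

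A reader might go further and infer that the trial has no serious-event procedure at all. The article cannot show that, because the full protocol is not available. Severity is low to moderate: a safety-wording correction with no effect on sample size, power or analysis.

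**What to change.** In the Adverse events section, limit the watch-then-refer rule to non-serious adverse events. Add that serious or severe events are referred to the trial paediatrician and senior investigator on receipt of the report, whether or not they persist. If the full protocol already has a serious-event procedure, cross-refer to it instead. The clinical response remains the paediatrician's decision.

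The cost is one or two sentences. The weekly diary review, the log and the paediatrician are already in place. The downside is an occasional prompt referral that proves unrelated to the supplements.
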